##### Overall treatment effect

2.5.2.3

The OTE scale will evaluate participants’ perceived overall improvement in dyspeptic symptoms and quality of life during the clinical trial. Participants will rate their improvement on a 15-point scale ranging from “extremely worsened” to “no change” to “completely improved” (22).

##### Dyspepsia VAS

2.5.2.4

Participants will assess their subjective dyspepsia severity over the past 2 weeks using a horizontal VAS marked from 0 to 100, where 0 indicates no discomfort and 100 indicates the worst imaginable discomfort. Participants scoring below 40 at screening will be excluded.

##### Functional dyspepsia-related quality of life

2.5.2.5

The FD-QoL questionnaire will assess the quality of life in dyspeptic patients across four domains: eating, vitality, emotions, and social functioning. It consists of 21 items rated on a 5-point Likert scale, with higher scores indicating better quality of life. Total and domain-specific scores will be calculated (23).

##### Spleen qi deficiency questionnaire

2.5.2.6

This questionnaire, which assesses appetite, food intake, and general fatigue, consists of 11 items rated on a 5-point scale (0–4). Participants will self-report on nine items, while two items (tongue and pulse diagnosis) will be assessed by a Korean medicine practitioner (24). Scores will be weighted and summed, then divided by four to obtain a total score. Scores exceeding the optimal cutoff of 43.18 will indicate Spleen Qi Deficiency (25).

##### Stomach qi deficiency questionnaire

2.5.2.7

This questionnaire includes 12 items related to inherent, dietary, and deficiency factors, rated on a 5-point scale (0–4). Participants will self-report on nine items, while three items (abdominal, tongue, and pulse diagnosis) will be assessed by a practitioner. The total score will be calculated, with scores exceeding 14 indicating Stomach Qi Deficiency (26).

##### Food retention questionnaire

2.5.2.8

This 17-item questionnaire will assess the presence of food stagnation using a 7-point Likert scale (1–7). Scores exceeding 51 will indicate food stagnation in FD patients (27).

##### Cold–heat pattern questionnaire

2.5.2.9

This self-report questionnaire will include eight items for Cold Syndrome and seven items for Heat Syndrome, rated on a 5-point scale based on typical symptoms over the past 6 months. Scores will be used to classify participants as having Cold Syndrome, Heat Syndrome, Mixed Cold–Heat Syndrome, or Absence of Cold–Heat Syndrome (28).

##### Deficiency–excess pattern questionnaire

2.5.2.10

Developed through four rounds of Delphi surveys, this questionnaire will include 11 items related to deficiency and excess, with seven items for Deficiency Syndrome and four items for Excess Syndrome. Scores for each item will be summed to calculate deficiency and excess scores (29).

##### Standard tool for pattern identification of FD

2.5.2.11

Developed based on literature reviews and expert consensus, this 36-item tool will assess participants’ health status over the past 2 weeks in relation to functional dyspepsia. Scores will be weighted to classify participants into six pattern types: spleen and stomach deficiency and cold, dampness and heat in the spleen and stomach, tangled cold and heat, spleen deficiency with qi stagnation, liver–stomach disharmony, and food retention disorder (11).

#### Safety evaluation variables

2.5.3

Liver function tests (AST, ALT) and renal function tests [blood urea nitrogen (BUN), creatinine (Cr)] will be conducted at screening and at week 8, requiring participants to fast for at least 8 h beforehand. Vital signs, including blood pressure (systolic and diastolic), pulse rate, and body temperature, will be measured. Blood pressure and pulse rate will be recorded in a seated position using an electronic sphygmomanometer after a minimum of 3 min of rest, except during telephone visits. Body temperature will be measured with an electronic thermometer after blood pressure measurement. Adverse events will be collected through participant self-reporting or investigator observation during the clinical trial.

#### Exploratory evaluation variables

2.5.4

Korean medicine diagnostic devices, including an HRV analyzer, tongue diagnosis device, pulse analyzer, and abdominal examination device, will be used. HRV is a non-invasive tool for assessing health status by measuring sympathetic and parasympathetic activity. Kyung Hee University Hospital at Gangdong will use the SA-6000 (MEDICORE Co., Ltd., Republic of Korea), while Dongguk University Ilsan Oriental Medical Hospital will use the SA-3000NEW (MEDICORE Co., Ltd., Republic of Korea). The tongue diagnosis system (CTS-2000, Daeseong Medical Device, Republic of Korea) will evaluate tongue coating thickness, distribution, and color. The pulse analyzer (DMP-Lifeplus, Daeyo Medi Co., Ltd., Republic of Korea) will provide cardiovascular and pulse wave information. The abdominal examination device (Digital Algometer FPX25, Wagner Instruments, United States) will assess tenderness at nine abdominal acupoints: CV-14, CV-12, left/right ST-20, left/right ST-25, CV-4, and left/right ST-28. Stool and saliva samples will be collected at baseline (week 0) and post-treatment (week 8) for gut microbiome and fecal metabolite profiling and for oral microbiome analysis, respectively.

### Data management

2.6

All study data will be collected by trained research staff and entered into a secure, password-protected electronic Case Report Form (eCRF) system developed for this trial. The eCRF system includes built-in logic checks and range validations to minimize data entry errors at the point of entry.

Data quality will be regularly monitored by the data management team. Source data verification will be performed by monitors. Queries will be issued for any missing, inconsistent, or outlying data points, and resolved by the site investigators. An electronic audit trail will be maintained to record all changes made to the database.

Participant confidentiality will be strictly maintained. Data will be pseudonymized, with identifying information stored separately and securely on institutional servers, accessible only to authorized personnel. The database will be locked after data cleaning and verification are complete, prior to statistical analysis.

### Sample size calculation

2.7

Participants will be randomly assigned to either the ACCORD group, which will receive YJT, PWS, or SST based on the machine learning–driven prediction, or the DISCORD group, which will not use the machine learning-based prediction for herbal assignments. Based on preliminary clinical trial results (19), the mean change in the GIS score after 8 weeks in both the ACCORD and DISCORD groups is assumed to be 2.72, with a standard deviation of 4.57. To meet this requirement, each group will require 45 participants. Considering a 10% dropout rate, the total required sample size is 100 participants. This sample size was determined for the prespecified primary comparison (ACCORD vs. pooled DISCORD) and was not inflated to power subgroup or stratified analyses, which will be considered exploratory.

### Statistical analysis

2.8

All statistical analyses will be conducted using two-sided tests with a significance level of 5%. For continuous data, means and 95% confidence intervals will be presented, whereas categorical data will be presented as frequencies and percentages. All analyses will be performed using SAS® Version 9.4 (SAS Institute Inc., Cary, NC, United States).

#### Demographic, sociological data, and other pre-treatment participant characteristics

2.8.1

Summary statistics for demographic and sociological variables, as well as pre-treatment participant characteristics, will be presented for each group. Depending on the normality of the data distribution, continuous variables will be analyzed using either the paired t-test or the Wilcoxon signed-rank test, whereas categorical variables will be analyzed using the chi-square test or Fisher’s exact test. If baseline characteristics show statistically significant differences between groups despite randomization, these variables will be included as covariates in the Mixed Model for Repeated Measures (MMRM) for the primary efficacy analysis to statistically adjust for potential confounding effects.

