#### Randomization and blinding

2.1.2

Participants will be divided into the ACCORD group, assigned herbal medication by the machine learning-based prediction algorithm, and the DISCORD group, which will not use the prediction algorithm. For example, if the prediction algorithm assigns YJT, the group receiving YJT will constitute the ACCORD group, whereas those receiving PWS or SST will constitute the DISCORD groups. Randomization will be stratified by each herbal medicine using block randomization to minimize bias before the clinical trial begins. For each stratification factor, the group allocation ratio will be 1:1 (ACCORD: DISCORD), with block sizes of 4 and 8. The DISCORD group will then be divided into two subgroups, excluding the optimal herbal medicine per the prediction algorithm, and randomly assigned, resulting in a 2:1:1 allocation (ACCORD: DISCORD_1: DISCORD_2). To prevent bias toward a specific herbal medicine, the maximum number of participants assigned to any single herbal medicine will be capped at 48. Any additional participants for that medicine will be excluded during screening.

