#### Statistical analysis and evaluation of efficacy endpoints

2.8.2

The primary efficacy endpoint is the between-group difference in the GIS score at week 8 (ACCORD vs. DISCORD). The primary endpoint will be analyzed using the MMRM, with treatment group and visit time as fixed factors and participant as a random factor.

The secondary efficacy endpoints include TDS, AR for dyspepsia, OTE, dyspepsia VAS, FD-QoL, Spleen Qi Deficiency Questionnaire, Stomach Qi Deficiency Questionnaire, Food Retention Questionnaire, Cold–Heat Pattern Questionnaire, and Deficiency–Excess Pattern Questionnaire. Categorical secondary variables will be analyzed using the chi-square test or Fisher’s exact test.

To address the issue of multiple comparisons for the multiple secondary efficacy endpoints, the Benjamini-Hochberg procedure (False Discovery Rate, FDR) will be applied to adjust the *p*-values. The primary endpoint will be tested at a significance level of 0.05 without adjustment. Exploratory outcomes will not be adjusted for multiplicity, and their results will be interpreted as hypothesis-generating.

Exploratory subgroup analyses (by assigned herbal formula and by DISCORD subgroup) will be performed to assess the consistency of treatment effects; these analyses are hypothesis-generating and are not powered for confirmatory inference. Effect modification will be explored using treatment-by-subgroup interaction terms within the mixed model, and results will be reported as effect estimates with 95% confidence intervals and interpreted cautiously.

For the primary outcome, missing data will be handled using the last observation carried forward (LOCF) method. In addition, multiple imputation will be applied as a sensitivity analysis to assess the robustness of results under different assumptions regarding missingness. The main analyses will be conducted on an intention-to-treat basis, with per-protocol analyses performed for comparison.

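### Covariates for the primary model are chosen by significance tests of baseline differences, using paired tests on independent arms, while baseline GIS and the randomisation stratum are not prespecified

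*Protocol article*

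**What the plan says.** Three parts of the protocol article together determine which covariates the primary model contains.

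- **Section 2.8.1 (pre-treatment characteristics).** For baseline comparisons, "continuous variables will be analyzed using either the paired t-test or the Wilcoxon signed-rank test", depending on normality; categorical variables get chi-square or Fisher tests. The results then feed the primary analysis: "If baseline characteristics show statistically significant differences between groups despite randomization, these variables will be included as covariates in the Mixed Model".
- **Section 2.8.2 (efficacy endpoints).** The primary endpoint is the ACCORD versus DISCORD difference in GIS at week 8. It is analysed by MMRM "with treatment group and visit time as fixed factors" and participant as random. Neither baseline GIS nor any stratification factor is named.
- **Section 2.1.2 (randomisation).** "Randomization will be stratified by each herbal medicine using block randomization to minimize bias before the clinical trial begins". The example given there shows that the stratum is the formula the algorithm recommends, which has three levels.

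Section 2.1.1 describes a parallel-group design, and Table 1 schedules GIS at screening, week 4 and week 8, so there is a single pre-treatment GIS value.

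**The concern.** There are three linked faults, all in what the text states and not in what it leaves out.

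1. **The rule chooses covariates by chance.** After correct randomisation, each between-arm baseline test is significant about 5% of the time whatever the variable. Significance says nothing about whether the variable predicts week-8 GIS. The list of candidates is open, so the primary model is known only once the data are in.
2. **The tests do not fit the comparison.** Paired t and signed-rank tests need matched observations. ACCORD and DISCORD participants are different people and no pairing is defined. The tests cannot be run if arm sizes differ, and with equal sizes the answer depends on the order of the records.
3. **The covariates that matter are not fixed.** Baseline GIS is the pre-treatment value of the endpoint, yet it can enter only through the rule. The recommended formula is balanced by blocking within strata, so the rule is unlikely ever to select it. If the stratum is prognostic, leaving it out makes the standard error too large. That is plausible, because section 2.1.1 says the algorithm uses baseline data to predict GIS change.

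At stake are the precision of the single primary comparison and the claim that its model was prespecified.

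**Working it through.** **Inputs from the protocol article**

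- Two-sided 5% tests (section 2.8).
- Effect assumed in section 2.7: "the mean change in the GIS score after 8 weeks in both the ACCORD and DISCORD groups is assumed to be 2.72".
- The SD given in section 2.7 is 4.57.
- Size stated in section 2.7: "each group will require 45 participants"; 10% dropout; 100 in total.
- Allocation 1:1 within strata (section 2.1.2).

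**Assumptions, because the article gives no figure**

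- Power of 80%.
- 2.72 read as the between-group difference.
- Baseline to week-8 GIS correlation r of 0.3 to 0.7, with equal variances at the two times.
- Number of baseline variables tested: 5 to 30, independent of each other.

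**Step 1: the plan's own sample size.** n per arm = 2(1.960 + 0.842)² × 4.57² / 2.72² = 44.3, rounded up to 45. Then 45 / 0.90 = 50 per arm, 100 in total. The stated size is reproduced. At 90% power the answer would be 60 per arm, so 80% is the reading that fits. Power at 45 per arm is 80.6% by the normal approximation and 79.7% by the t distribution, so there is no margin.

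**Step 2: how often the rule is triggered.** P(at least one significant) = 1 − 0.95^k:

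| k variables | 5 | 10 | 20 | 30 |
|---|---|---|---|---|
| Probability | 23% | 40% | 64% | 79% |

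At k = 20 the expected number is 20 × 0.05 = 1. A value near 20 is realistic. The article names 4 vital signs, 4 laboratory tests, 4 symptom or quality-of-life scores (GIS, TDS, VAS, FD-QoL), 3 questionnaires (spleen qi, stomach qi, food retention) and 4 pattern scores (cold, heat, deficiency, excess). That is 19 before demographics and device readings.

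**Step 3: variance saved by adjusting for baseline GIS.**

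- Against the raw week-8 score the ratio is 1 − r²: 0.91, 0.75, 0.51 at r = 0.3, 0.5, 0.7, a saving of 9%, 25%, 49%.
- Against change from baseline it is (1 − r²) / [2(1 − r)] = (1 + r)/2: 0.65, 0.75, 0.85, a saving of 35%, 25%, 15%.

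**Step 4: power at 45 per arm (normal approximation).** Section 2.7 does not say clearly whether 4.57 is the SD of the week-8 score or of the change, so both are shown. The adjusted SD is the week-8 SD × √(1 − r²). If 4.57 is the SD of change, the week-8 SD is 4.57 / √[2(1 − r)].

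| Reading of 4.57 | r | Week-8 SD | Unadjusted power | Adjusted SD | Adjusted power |
|---|---|---|---|---|---|
| Week-8 score | 0.3 | 4.57 | 80.6% | 4.36 | 84% |
| | 0.5 | 4.57 | 80.6% | 3.96 | 90% |
| | 0.7 | 4.57 | 80.6% | 3.26 | 98% |
| Change | 0.3 | 3.86 | 92% | 3.68 | 94% |
| | 0.5 | 4.57 | 81% | 3.96 | 90% |
| | 0.7 | 5.90 | 59% | 4.21 | 87% |

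**Step 5: the rule itself.** Simulation of the week-8 comparison with one baseline covariate, 45 per arm, week-8 SD 4.57, 20,000 runs per setting. The rule is modelled with a two-sample baseline test.

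| | r = 0.3 | r = 0.5 | r = 0.7 |
|---|---|---|---|
| Type I error, test then adjust | 4.8% | 4.2% | 3.6% |
| Type I error, always adjust | 5.2% | 4.8% | 5.2% |
| Power, test then adjust | 80% | 81% | 82% |
| Power, always adjust | 83% | 89% | 97% |
| Type I error when the baseline p-value is 0.05 to 0.20, so the rule does not adjust | 6.6% | 8.7% | 10.9% |

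**Step 6: the paired test.** With equal arms paired in arbitrary order, the paired t-test still rejects about 5% of the time. It flags only about 86% of the imbalances that the two-sample test flags, so chance ordering changes which covariates enter.

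**The case against.** The strongest case against concerns weight and wording.

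- **Validity is not lost overall.** Type I error stays at or below 5%, and power under the rule stays at about the level that reproduces 45 per arm. This stands. The harm is forgone precision, a conditional error rate above nominal when imbalance falls just short of significance, and a model not fixed in advance.
- **Baseline GIS may be partly used.** If the screening GIS were one of the response visits in the MMRM, baseline would carry some information and the gains in step 4 would not apply as shown. The text does not say so and names no group-by-visit term, so this reading is unsupported. It is still fair to say that baseline GIS is not prespecified, since the rule could admit it.
- **The paired tests may be a copying slip.** Section 2.8.3 uses the same pair of tests for pre–post safety changes, where they are right. That is probable, but in section 2.8.1 the tests decide what enters the primary model, so they still need correcting.
- **The sizes rest on assumptions.** The article gives neither the number of variables nor the GIS correlation, and overlapping questionnaires are not independent. This stands, hence the ranges. The comparison with change is also secondary, because section 2.8.2 specifies the week-8 score.
- **The stratum gain is unquantified.** This stands: no between-stratum variance is given, and a weakly prognostic stratum would matter little.

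An unseen analysis plan does not answer the point, because the article itself states both the model terms and the rule for changing them.

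**Conclusion.** The concern holds. The article commits the primary analysis to a data-driven covariate rule, names tests that do not suit independent arms to operate it, and does not prespecify baseline GIS or the stratum used in randomisation.

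- The chance that some covariate enters by accident is 64% with 20 independent variables, and 23% to 79% over 5 to 30.
- Reading 4.57 as the week-8 SD, always adjusting for baseline GIS in place of the rule raises simulated power by about 3, 9 or 16 percentage points at correlations of 0.3, 0.5 or 0.7 (from unrounded results).
- Reading 4.57 as the SD of change, an unadjusted week-8 comparison has as little as 59% power at correlation 0.7, against 87% with adjustment.
- Overall type I error is not inflated. The effect of omitting the stratum cannot be sized from the article.

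These figures are for a single week-8 comparison with one covariate, not the full repeated-measures model.

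**What to change.** 1. In section 2.8.1, delete the sentence that adds significantly different baseline variables to the MMRM.
2. In section 2.8.2, name baseline (screening) GIS and the algorithm-recommended formula (three levels) as fixed covariates of the primary model. Site may be added; section 2.1.2 does not name it as a stratification factor, so this is optional.
3. State in section 2.8.2 that screening GIS is a covariate and which visits are responses.
4. Present the baseline table descriptively. If between-group tests are kept, name the independent-samples t-test and the Wilcoxon rank-sum test, and do not let them choose covariates.

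**Cost.** Wording only, through the amendment route in section 2.11. All the variables are already collected. The covariates use 1 (baseline GIS) + 2 (formula) + 1 (site) = 4 degrees of freedom out of about 90, and the total of 100 need not change. The change has to be made before outcome data are examined if the covariates are to count as prespecified.

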#### Statistical analysis and evaluation of efficacy endpoints

2.8.2

The primary efficacy endpoint is the between-group difference in the GIS score at week 8 (ACCORD vs. DISCORD). The primary endpoint will be analyzed using the MMRM, with treatment group and visit time as fixed factors and participant as a random factor.

The secondary efficacy endpoints include TDS, AR for dyspepsia, OTE, dyspepsia VAS, FD-QoL, Spleen Qi Deficiency Questionnaire, Stomach Qi Deficiency Questionnaire, Food Retention Questionnaire, Cold–Heat Pattern Questionnaire, and Deficiency–Excess Pattern Questionnaire. Categorical secondary variables will be analyzed using the chi-square test or Fisher’s exact test.

To address the issue of multiple comparisons for the multiple secondary efficacy endpoints, the Benjamini-Hochberg procedure (False Discovery Rate, FDR) will be applied to adjust the *p*-values. The primary endpoint will be tested at a significance level of 0.05 without adjustment. Exploratory outcomes will not be adjusted for multiplicity, and their results will be interpreted as hypothesis-generating.

Exploratory subgroup analyses (by assigned herbal formula and by DISCORD subgroup) will be performed to assess the consistency of treatment effects; these analyses are hypothesis-generating and are not powered for confirmatory inference. Effect modification will be explored using treatment-by-subgroup interaction terms within the mixed model, and results will be reported as effect estimates with 95% confidence intervals and interpreted cautiously.

For the primary outcome, missing data will be handled using the last observation carried forward (LOCF) method. In addition, multiple imputation will be applied as a sensitivity analysis to assess the robustness of results under different assumptions regarding missingness. The main analyses will be conducted on an intention-to-treat basis, with per-protocol analyses performed for comparison.

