The ground truth (target variable) for model training was the observed change in the Gastrointestinal Symptom (GIS) score from baseline to 8 weeks in the preliminary study. The models were trained using comprehensive baseline data as input features. These features included demographics (e.g., age, sex, and FD duration); patient-reported outcomes and questionnaires (e.g., GIS, and various pattern identification questionnaires); data from Korean medicine diagnostic devices (e.g., tongue diagnosis system, radial pulse analyzer, and digital algometer readings); and laboratory test results (e.g., blood chemistry).

During development, the dataset was split into training (80%) and test (20%) sets for internal validation. Hyperparameter tuning was conducted using RandomizedSearchCV with 5-fold cross-validation on the training data. To mitigate overfitting due to high data dimensionality, an iterative feature selection process was employed to enhance model robustness. The final models demonstrated robust predictive accuracy on the independent test set, confirming their capability to predict treatment responses and discriminate the relative effectiveness among the herbal formulations. Detailed methodology of the algorithm development is provided in Supplementary material 1. The algorithm for prediction system employed in this trial is a locked version (v1.1) that will not be updated during the study period. The prospective validation of this locked algorithm in a new cohort is essential for evaluating its generalizability and mitigating potential biases or overfitting inherent in the preliminary training dataset.

All groups will take the assigned clinical trial medications for 8 weeks. Participants will attend clinic visits at 4-week intervals until week 8 for evaluation of clinical variables, including vital signs, questionnaire surveys, and assessments with Korean medicine diagnostic devices (heart rate variability [HRV], tongue diagnosis, pulse diagnosis, and abdominal diagnosis). In addition, telephone visits will be conducted at 2-week intervals (weeks 2 and 6) to assess whether FD-related pain or discomfort has moderately improved since the previous treatment (Figure 1). Before and after taking the herbal medicine, blood samples (at screening and week 8) and stool and saliva samples (at weeks 0 and 8) will be collected to analyze blood and fecal metabolites as well as gut and oral microbiomes. A detailed assessment schedule is provided in Table 1.

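### The primary endpoint is the week-8 GIS score in section 2.8.2 but the 8-week GIS change in section 2.7, so the SD of 4.57 used for sizing is not the SD of the endpoint as stated

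*Protocol article*

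**What the plan says.** Section 2.8.2 gives the formal definition: "The primary efficacy endpoint is the between-group difference in the GIS score at week 8 (ACCORD vs. DISCORD"). The analysis is an MMRM with treatment group and visit as fixed factors and participant as a random factor. Neither change from baseline nor a baseline GIS term is mentioned there.

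Section 2.8.1 allows a baseline variable into that model only if it turns out to differ significantly between the groups.

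Section 2.7 rests on a different variable: "the mean change in the GIS score after 8 weeks in both the ACCORD and DISCORD groups is assumed to be 2.72". The same sentence attaches an SD of 4.57 to that change. From this it concludes that "each group will require 45 participants", or 100 in total with 10% dropout.

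Section 2.1.1 says the algorithm was trained on "the observed change in the Gastrointestinal Symptom (GIS) score from baseline to 8 weeks in the preliminary study". The abstract and section 2.5.1 name only the GIS instrument, so they do not settle which variable is primary. Table 1 has GIS at screening (Visit 1), week 4 and week 8.

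**The concern.** A sample size holds for the variable whose SD went into it. As section 2.7 reads, 4.57 is the SD of a within-patient change, whereas section 2.8.2 reads as a comparison of week-8 scores that is normally unadjusted for baseline. These two SDs are generally different. The statement in the Discussion that the trial was powered for the comparison of ACCORD with pooled DISCORD is therefore not established for the endpoint as worded.

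There is also a question of pre-specification. With two candidate primary variables in print, and baseline adjustment dependent on a significance test, score or change could be chosen after the data are seen. The expected treatment difference is the same either way, but the estimate and p-value in a given sample of 100 patients are not.

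**Working it through.** **Inputs.** Two-sided 5% level (section 2.8). 1:1 allocation (section 2.1.2). SD 4.57 and 45 per group (section 2.7). Power is not stated in the article, so 80% is assumed. Section 2.7 attributes 2.72 to both groups. It is taken here as the intended between-group difference, because that reading gives 45.

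**Step 1: reproduce the stated size.**
n = 2 × (4.57/2.72)² × (1.960 + 0.842)² = 44.3, rounded up to 45 per group. Then 45/0.9 = 50 per group, 100 in total. At 85% power the formula gives 51 and at 90% it gives 60, so 80% is the level that fits. Two-sample t-test power at 45 per group is 79.7%. The arithmetic is sound for a variable with SD 4.57.

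**Step 2: link the SD of change to the SD of the week-8 score.** Let the screening and week-8 scores have a common SD s and correlation r. Then
Var(change) = 2s²(1 − r) = 4.57², so s = 4.57/√(2(1 − r)).
This equals 4.57 only at r = 0.5. Below that the raw score is less variable than the change, and above it more variable.

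**Step 3: SD if screening GIS is a covariate.**
Residual SD = s√(1 − r²) = 4.57 × √((1 + r)/2).
This is below 4.57 for every r below 1. With screening GIS in the model, score and change give the same treatment contrast, because they differ only by a quantity already in the model.

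**Step 4: power at 45 per group for a difference of 2.72** (t-test, two-sided 5%; one further degree of freedom is used in the adjusted case).

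| r | SD of week-8 score | Power, unadjusted week-8 score | Residual SD, adjusted | Power, adjusted |
|---|---|---|---|---|
| 0.3 | 3.86 | 91% | 3.68 | 93% |
| 0.5 | 4.57 | 80% | 3.96 | 90% |
| 0.6 | 5.11 | 70% | 4.09 | 88% |
| 0.7 | 5.90 | 58% | 4.21 | 86% |
| 0.8 | 7.23 | 42% | 4.34 | 84% |

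Unadjusted change has SD 4.57 and power of about 80% at every r.

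**Step 5: required size for the unadjusted score at 80% power.** By the formula of step 1, r = 0.3 needs 32 per group, r = 0.5 needs 45 and r = 0.7 needs 74.

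**The case against.** The strongest reply is that the sentence in section 2.7 is garbled. If 2.72 cannot be taken literally as the change in both groups, it is selective to take 4.57 literally as the SD of change. This stands in part. That 4.57 belongs to the change is how the sentence reads, but the preliminary study that would confirm it is not shown.

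Second, a reader might infer that the trial is underpowered. The documents do not support that. They give neither r nor the SD of the week-8 score, and power on the raw score is at or above about 80% for r up to 0.5. The calculation is also a single-time-point t-test, whereas the stated analysis is an MMRM that includes the week-4 data.

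Third, a reader might infer that the trial tests something other than what the algorithm predicts, since training used the change. That does not follow. Under randomisation the expected between-group difference is the same for score and change; only precision differs.

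Fourth, how baseline enters an MMRM is detail that an article may leave to the full protocol or analysis plan. If that document always adjusts for screening GIS, the problem largely disappears and 4.57 is conservative. But this article does state the endpoint, the model terms and a conditional covariate rule, and together they point to an unadjusted week-8 comparison.

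Lastly, Table 1 labels Visit 2 as baseline although GIS is collected at Visit 1. This creates no real ambiguity, because screening is the only pre-treatment GIS.

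**Conclusion.** The inconsistency holds: sections 2.7 and 2.8.2 use different variables, and nothing in the article reconciles them. As written, the sizing SD belongs to the change and not to the unadjusted week-8 score.

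Its size cannot be fixed from the documents. For r from 0.3 to 0.7, power at 45 per group on the unadjusted score runs from 91% down to 58%, on either side of the 80% that reproduces the stated size. These figures assume equal variances at screening and week 8, 2.72 as the between-group difference, and 4.57 as the SD of change. Neither a power shortfall nor an error in 45 per group is shown. The point is worth correcting because it leaves the primary variable open and the power statement unsupported for the endpoint as worded.

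**What to change.** In sections 2.7 and 2.8.2, name one primary variable: change in GIS from the screening (Visit 1) score to week 8. In section 2.8.2, state that screening GIS is always a covariate in the MMRM, whatever the baseline comparison in section 2.8.1 shows. The stated 45 per group can then remain, with 4.57 described as a conservative SD.

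If the unadjusted week-8 score is kept as the endpoint, replace 4.57 in section 2.7 with the SD of the week-8 score from the preliminary study and restate the power at 45 per group. That figure may be less favourable than the present one.

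The first option costs only wording and an amendment, with no new patients, visits or measurements, since screening GIS is already collected. It should be settled before any outcome data are examined by group.
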